#### Data monitoring body

The data will be prospectively entered into a dedicated online database designed and maintained by the Clinical Trials Unit of La Paz University Hospital, which belongs to the Spanish Clinical Research Network. The entire process is governed by the principles of European biomedical research regulations, which ensure confidentiality. In accordance with European regulations and the International Conference of Harmonisation Good Clinical Practice Guidelines, the investigators and the institution will provide direct access to the authorised representatives of the ethics committees in the event that the original patient records are required for verification of the study data and procedures.

#### Sample size estimates

There have been no previous studies using CGM devices to assess the dynamics of glucose levels in patients treated with MT, which would allow a formal calculation of the sample size. Furthermore, the proportion of patients in whom technical failures may impede the recording of glycaemia at the time of reperfusion remains unknown. Using previous studies,^29 30^ if we consider a 15% loss to sensor failure or loss to follow-up, we can calculate, with an alpha risk of 0.05, a beta risk of 0.20 and an estimated difference in death-dependence of 30%, that it is recommended a sample size of 50 patients per group be used, taking into account that the death-dependence ratio in the control group might be 0.66 (according to GLIAS-II data). However, given that the actual percentage of possible technical failures of the sensor is unknown, we propose to perform an intermediate analysis and recalculate the sample size after the inclusion of 50 patients. The inclusion of 100 patients over a 2-year recruitment period is considered feasible, given that the number of MT procedures in our centre exceeds 100 per year. This sample size will allow us to investigate the differences in glycaemic levels at the time of reperfusion between patients with good or poor functional recovery at 3 months. After enrolling 100 patients, further power calculations will be performed to estimate the sample size for future studies. Recruitment began on 30 August 2023 and is ongoing.

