## Introduction

 Poststroke hyperglycaemia is a very common complication in ischaemic stroke, affecting approximately two-thirds of patients, and is associated with poorer recanalisation rates, reduced perfusion, increased damage due to ischaemia-reperfusion and, consequently, poorer patient outcomes.^1 2^ Furthermore, hyperglycaemia can counteract the potential therapeutic effect of reperfusion treatments such as intravenous thrombolysis^3 4^ and mechanical thrombectomy (MT).^5^,^8^

Hyperglycaemia can cause damage through several pathophysiological mechanisms, including abnormalities in the blood–brain barrier and increased lactic acid production.^1 2^ Poststroke hyperglycaemia has been independently associated with poor outcomes after MT, with lower rates of functional recovery,^6 7 9^ a higher risk of haemorrhagic transformation^7 9 10^ and cerebral oedema^11 12^ and increased mortality at 3 months.^7^ The GLycemia in Acute Stroke (GLIAS) study was the first multicentre study to establish prognostic threshold for hyperglycaemia at 155 mg/dL, demonstrating a correlation between elevated glucose levels in the acute phase of stroke and poor outcomes, independently of stroke severity, infarct volume, diabetes or age.^13^

In patients treated with MT, the Solitaire Flow Restoration With the Intention for Thrombectomy (SWIFT) clinical trial showed that for each 10 mg/dL increase in blood glucose values, there was a 42% reduction in the probability of an excellent recovery at 3 months.^6^ It has yet to be determined whether administering insulin therapy prior to and during MT can mitigate the negative impact of hyperglycaemia in stroke recovery. Several studies have attempted to analyse this impact based on retrospective discrete determinations, such as glycaemia on admission^5 7 8 14^ and 24–48 hours after stroke,^15^,^17^ but none of them have monitored glycaemia during the MT procedure.

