#### Intervention

Patients who meet the inclusion criteria and none of the exclusion criteria will be invited to participate in this research study. The attending stroke neurologist will provide and explain the study information document to the patient (or to the patient’s family member if the patient is unable to give consent personally). This informed consent process will take place in parallel with the preparation of the MT and will not delay any therapeutic procedure. Whenever the informed consent has been signed by a family member and once the patient is able to consent, the patient will be informed about the research study and given the opportunity to reconsider or withdraw.

After signing the informed consent document and before starting the MT procedure, a subcutaneous CGM device will be placed, removing it on day 15 or at discharge, whichever comes first. CGM will be performed using a Freestyle Libre ProIQ device (FSL-CGM, Abbot Diabetes Care, Alameda, California, USA), which was selected from those currently available on the market, with previous studies documenting its safety and suitability for radiological procedures.

All patients will be managed according to current guidelines for the diagnosis and treatment of stroke, including the administration of thrombolytics if the established criteria for this treatment are met. Anaesthetic management, including the choice of general anaesthesia or conscious sedation, will follow the local protocols of the anaesthesiology department. Patients with glucose levels >155 mg/dL will receive insulin at the discretion of the attending physician, following the local protocols for managing hyperglycaemia in hospitalised patients and the guidelines for managing hyperglycaemia in patients with stroke (online supplemental table 1). Patients who underwent only angiography without MT treatment due to evidence of complete revascularisation at the time of arteriography will be excluded from the analysis.

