#### Data collection and management

Glucose levels at the time of reperfusion in patients achieving thrombolysis in cerebral infarction (TICI) -2b, TICI-2c or TICI-3 recanalisation pattern after MT.mRS at 3 months. Its dichotomised assessment (mRS 0–2 indicating good functional recovery and 3–6 indicating death or dependency) is commonly used in acute stroke trials.Related to glycaemic control:Peak interstitial glucose levels during the MT procedure.Total time with interstitial glucose levels above 155 mg/dL from arrival in the emergency department to arterial recanalisation.Time with interstitial glucose levels in the range of 110–154 mg/dL: (a) from arrival at the emergency department to recanalisation; (b) during the first 24 hours and (c) during hospitalisation.Proportion of patients receiving insulin therapy for poststroke hyperglycaemia during the first 24 hours after onset of stroke symptoms.Insulin therapy received in clinical practice (time, route and dose).Number of CGMs with technical failures (missing or interrupted readings) or requiring replacement due to involuntary device removal or inadequate implantation.Additional CGM device data: mean interstitial glucose level, coefficient of variation.Related to MT:The number of MT passes (including aspiration and stent retriever passes).Degree of recanalisation according to TICI classification on final angiogram.Blood pressure in the emergency department and at the time of reperfusion.Related to stroke:Infarct size at 24 hours (assessed by a neuroradiologist who will be unaware of the glucose monitoring data).Haemorrhagic transformation at 24 hours (assessed by a neuroradiologist who will be unaware of the glucose monitoring data) is categorised into four types: (1) haemorrhagic infarction type 1 (HI-1)—small petechiae at the edges of the infarct area; (2) HI-2—confluent petechiae in the infarct area without mass effect; (3) parenchymal haematoma type 1 (HP-1)—haematoma occupying ≤30% of the infarct area with discrete mass effect and (4) parenchymal haematoma type 2 (HP-2)—haematoma occupying >30% of the infarct area with obvious mass effect.Symptomatic haemorrhagic transformation is defined as CT/MRI evidence of any type of haemorrhage associated with neurological deterioration ≥4 points on the NIHSS scale from baseline or leading to death.NIHSS score at 24 hours, at hospital discharge and at 3 months.Neurological or systemic complications during follow-up. The following complications will be systematically assessed at each visit: coma, seizures, early neurological deterioration, cerebral oedema, recurrent stroke, acute coronary syndrome, pulmonary thromboembolism, respiratory infection, urinary tract infection, sepsis and local haematoma or infection at the insertion site of the subcutaneous glucose monitor. Any other complication reported or detected during follow-up will be also recorded.Distribution of mRS scores at 90 days.Mortality at 3 months.Biomarkers of ischaemia-reperfusion injury: miR-29b, miR-339, miR-15a, miR-100 and miR-424. Samples will be drawn at the time of reperfusion and 24 hours later.Demographics: age, sex, race, weight, height, diabetes, hypertension, dyslipidaemia, coronary disease, atrial fibrillation, metabolic syndrome, chronic kidney disease with an estimated Glomerular Filtration Rate (eGFR)<60 mL/min/1.73 m^2^, smoking and alcohol abuse.Previous drug therapy: antiplatelets, anticoagulants, antihypertensives, antidiabetics and lipid-lowering agents.Stroke data: date of symptom onset (or last asymptomatic event in patients with unknown stroke onset), aetiological subtype of stroke and treatment with intravenous thrombolysis.Vital signs and laboratory values on admission at the emergency department: temperature, blood pressure, heart rate, respiratory rate, blood glucose and glycated haemoglobin.Treatment times: time from stroke onset to hospital admission; time from hospital admission to start of intravenous thrombolysis (door-to-needle time); time from hospital admission to start of MT (door-to-femoral puncture time); time from hospital admission to reperfusion; time from femoral puncture to reperfusion.Neuroimaging data: Baseline Alberta Stroke Programme Early CT Score, baseline collateral flow and baseline perfusion.

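### The 15% loss allowance uses up the whole sample-size margin but leaves out two further losses that the plan itself creates after enrolment

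*Protocol article*

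**What the plan says.** All references are to the protocol article.

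- **Sample size estimates.** The calculation is set up "with an alpha risk of 0.05, a beta risk of 0.20", with "an estimated difference in death-dependence of 30" percent, and assumes that "the death-dependence ratio in the control group might be 0.66 (according to GLIAS-II data"). The only losses named are those in "if we consider a 15% loss to sensor failure or loss to follow-up". The result is 50 per group. A recalculation is planned after 50 patients, and the reason given is that the rate of sensor failures is unknown.
- **Patient population (Table 1).** Consent and enrolment come before the endovascular procedure, so neither the performance of thrombectomy nor the final TICI grade is known at enrolment.
- **Intervention.** Patients who have angiography without thrombectomy "due to evidence of complete revascularisation at the time of arteriography will be excluded from the analysis".
- **Data collection and management.** The exposure is listed as "Glucose levels at the time of reperfusion in patients achieving thrombolysis in cerebral infarction" grade 2b, 2c or 3.
- **Statistical analysis.** The logistic regression for functional recovery at 3 months takes glucose at the time of reperfusion as its exposure.

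The article states no replacement of patients who turn out not to be evaluable.

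**The concern.** An allowance for loss should cover every route by which an enrolled patient can fail to reach the primary analysis. Here it covers two routes, and the plan has four. The two missing ones arise after enrolment: no thrombectomy because the vessel has already reopened, and a final TICI grade below 2b, which leaves the patient without a defined exposure.

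If the 15% had been generous, this would be a matter of wording. If it was fully used in getting from the required number to 100, any further loss takes the study below the number on which the 80% power rests. The planned recalculation could catch this, but its stated purpose is sensor failure alone.

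**Working it through.** **Inputs from the article:** alpha 0.05 (sidedness not stated, taken as two-sided), power 0.80, control-group rate 0.66, absolute difference 0.30 (so 0.66 v 0.36), equal groups, 15% loss, 100 enrolled.

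**Step 1. Reproduce the plan's figure.** Two proportions, pooled variance under the null, no continuity correction:

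n per group = [1.960 × √(2 × 0.51 × 0.49) + 0.842 × √(0.66 × 0.34 + 0.36 × 0.64)]² / 0.30²

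= [1.386 + 0.568]² / 0.09 = 42.4, rounded up to 43.

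42.4 / 0.85 = 49.9, which is the stated 50. (Rounding to 43 first gives 51 by division by 0.85, or 50 by multiplication by 1.15.) Other readings do not match after the 15%: a relative 30% reduction gives 116 per group, 0.66 v 0.96 gives 31, and a two-sided test with continuity correction gives 58.

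**Step 2. How much margin is left?** 100 × 0.85 = 85 evaluable, or 42.5 per group.

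Power = Φ{[0.30 × √42.5 − 1.386] / 0.674} = Φ(0.845) = 0.801.

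The required total is 2 × 42.4 = 84.8. The 15% therefore uses the whole margin. One further percent lost leaves 84.2 patients and power 0.797.

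**Step 3. Add the two uncounted losses.** The article gives no rate for either, so the combined further loss L is an assumption, applied to the 85 as if independent of the first 15%. Evaluable = 85 × (1 − L). The power formula is that of Step 2. Enrolment needed = 86 / [0.85 × (1 − L)], rounded up, where 86 = 2 × 43.

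| Assumed further loss L | Evaluable of 100 | Power, 0.66 v 0.36, equal groups | Enrolment needed for 86 evaluable |
|---|---|---|---|
| 0% | 85 | 0.80 | – |
| 5% | 80.8 | 0.78 | 107 |
| 10% | 76.5 | 0.76 | 113 |
| 15% | 72.2 | 0.73 | 120 |
| 20% | 68.0 | 0.71 | 127 |
| 25% | 63.8 | 0.68 | 135 |

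Put as a detectable difference, 72 evaluable patients in equal groups give 80% power for 32.5 points below 0.66 instead of 30.

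**The case against.** **There is no arithmetic error, and the authors are candid.** Both are true. The figure reproduces, and the section says that earlier studies do not allow a formal calculation. It nevertheless states alpha, beta, a difference and a loss allowance, and the allowance should match the plan's own exclusions.

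**The size of the shortfall is unknown.** This stands. A reader might infer that the primary analysis will fall far short of 85, but the article supports only a number below 85 by an unstated amount. Up to about 5% combined further loss, power stays within about 2 points of 80%.

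**The exclusions are narrow.** The Intervention section removes only angiography-only patients with complete revascularisation, not everyone who misses thrombectomy. The TICI wording is an item in a data-collection list, and the Statistical analysis section names no TICI restriction. Still, that item is the only definition given of the exposure in the regression, and a patient below TICI 2b has no value under it.

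**A recalculation after 50 patients is planned.** It is the most relevant mitigation. By then the counts of both losses should be known, but as written it addresses sensor failure only.

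**Restriction to reperfused patients follows from the research question.** Agreed. It is a legitimate target and only needs saying.

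Two stronger readings should not be drawn. A reader might infer selective loss of hyperglycaemic patients, because the Introduction says that hyperglycaemia "is associated with poorer recanalisation rates". That is a general background statement about ischaemic stroke. It shows neither the size nor the direction of any bias in this analysis. A reader might also add the effect of unequal exposure groups, but that is a separate matter and is not caused by the omitted losses.

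**Conclusion.** The point holds as a mismatch between the loss allowance and the plan's own exclusions. With 100 enrolled, the stated 80% power is met only if total loss stays at the 15% named for sensor failure and loss to follow-up. Any non-zero loss to prior revascularisation or to TICI below 2b takes the study under that basis. Under assumed combined further losses of 5% to 25%, about 81 down to 64 patients are evaluable and power is about 0.78 down to 0.68.

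These figures rest on assumed loss rates, equal groups and 0.66 v 0.36. They describe the two-proportion planning calculation. The primary analysis is a logistic regression on glucose levels, which the article does not say will be dichotomised, so its own power may differ. The issue is modest if the two losses are rare and material if they reach 10% or more.

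**What to change.** In Sample size estimates:

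1. State the expected evaluable number after all four losses (sensor failure, loss to follow-up, complete revascularisation at arteriography, TICI below 2b), with the rates assumed. Say whether 100 means enrolled or evaluable.
2. Restate the power, or the detectable difference, for that number.
3. Make the recalculation after 50 patients count every reason for non-evaluability, not sensor failure alone.
4. State that the primary estimate applies to patients reaching TICI 2b–3.

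This is rewording and needs no new data, since final TICI is already recorded. Recruitment is reported as ongoing, so the recalculation can still be widened if the first 50 patients have not yet been reviewed. The cost is a somewhat lower stated power, or a larger enrolment if 80% is to be kept (113 at an assumed 10% further loss, 127 at 20%).

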These miRNAs are of interest due to their functions, with previous studies demonstrating a role in cerebral ischaemia. In the context of ischaemic stroke, miR-339, miR-15a, miR-424 and miR-100 have been associated with large vessel occlusion.^33 34^ MiR-339, which is overexpressed in cases of cerebral and myocardial ischaemia,^35^ is related to neuronal survival and suppression of apoptosis in ischaemic conditions.^36^ MiR-15 and miR-424 have been linked to an antiangiogenic effect through VEGF inhibition.^37^ Additionally, miR-100 has been demonstrated to have an antiatherosclerotic effect.^38^ Furthermore, this miRNA exhibits varying levels in patients with cerebral infarction due to large vessel occlusion, suggesting a potential association with functional recovery.^33^ Finally, miR-29b has been demonstrated to attenuate ischaemic injury by negatively regulating the p53-dependent apoptosis pathway and could, therefore, be a potential target in diminishing cell injury in ischaemic stroke.^39^

We hypothesised that those patients with glycaemia values <155 mg/dL during MT and especially at the time of reperfusion will have less ischaemia-reperfusion injury, showing a different miRNA expression profile, with better neurological and functional outcomes and a lower risk of haemorrhagic transformation and cerebral oedema.

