### Statistical analysis

Statistical analysis will be conducted with the assistance of the Clinical Trials Unit of La Paz University Hospital. To analyse the continuous variables, the following information will be collected: the number of participants, mean, SD, median, minimum, maximum and 25th and 75th percentiles. For the categorical variables, the frequency distribution and 95% CI will be provided.

Multivariate logistic regression analyses will be performed to evaluate the effect of glucose levels at the time of reperfusion on functional recovery at 3 months, adjusting for other factors that show statistically significant differences in the univariate analysis. Significance will be assessed using the likelihood ratio.

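### The 80% power behind 50 patients per group holds only for an equal split and an unadjusted test; the groups are undefined and observed, and the stated analysis is an adjusted model on glucose level

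*Protocol article*

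**What the plan says.** All references are to the protocol article.

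- **Sample size estimates** gives the error rates ("with an alpha risk of 0.05, a beta risk of 0.20"), a 30% difference in death or dependence, and 15% loss to sensor failure or follow-up. It adds that "the death-dependence ratio in the control group might be 0.66", citing GLIAS-II, and concludes that "it is recommended a sample size of 50 patients per group be used". The two groups are not named.
- The same section then says that this sample size will serve to study "differences in glycaemic levels at the time of reperfusion between patients with good or poor functional recovery". It plans a recalculation after 50 patients and gives the unknown rate of sensor failure as the reason.
- **Statistical analysis** plans multivariable logistic regression "to evaluate the effect of glucose levels at the time of reperfusion on functional recovery at 3 months", adjusted for factors significant in univariate analysis.
- **Introduction** states the hypothesis for patients with "glycaemia values <155 mg/dL during MT and especially at the time of reperfusion". It also describes poststroke hyperglycaemia as "affecting approximately two-thirds of patients".
- **Randomisation** says there is none, and **Patient population** has no glucose criterion, stratum or quota.

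**The concern.** A figure of 50 per group with a beta risk of 0.20 tells the reader that the study has 80% power for its main question. That property depends on three things: two defined groups, equal sizes, and the test that will actually be run.

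Here the groups have to be inferred. Their sizes will be whatever the patients' own glucose values produce. The model in the analysis section is also not the comparison that was sized. One sample size is attached to outcome compared between groups, to glucose compared between outcome groups, and to an adjusted regression on glucose level.

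If the result is null, readers will judge it against a stated 80% that belongs to a different comparison. The planned recalculation would not correct this, because as described it responds only to sensor failure.

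**Working it through.** **Inputs from Sample size estimates:** alpha 0.05 (two-sided assumed; sidedness is not stated), power 0.80, control rate 0.66, difference 0.30, loss 15%, equal groups implied.

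**1. Reproduce the stated figure.** Two-proportion formula, pooled variance under the null, no continuity correction, with p1 = 0.66, p2 = 0.36 and mean 0.51:

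n = [1.960·√(2·0.51·0.49) + 0.842·√(0.66·0.34 + 0.36·0.64)]² / 0.30² = (1.386 + 0.568)² / 0.09 = 42.4 per group.

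Allowing for loss: 42.4 / 0.85 = 49.9, that is 50 per group. The figure reproduces.

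**2. Which reading of control gives 50?**

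| Reading | Rates | n per group | After 15% loss |
|---|---|---|---|
| Control is the worse-outcome group | 0.66 v 0.36 | 42.4 | 50 |
| Control is the better-outcome group | 0.66 v 0.96 | 25.6 | 30 |
| 30% is a relative reduction | 0.66 v 0.462 | 97.4 | 115 |

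Of these three, only the first matches. By inference, 0.66 belongs to the higher-glucose patients, but the text does not say so.

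**3. Power of a two-group contrast at other splits.** Evaluable patients: 100 × 0.85 = 85. Power = Φ[(0.30 − 1.960·SE0) / SE1], where SE0 is the pooled and SE1 the unpooled standard error. The larger group is given 0.66.

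| Split | SE0 | SE1 | Power |
|---|---|---|---|
| 1:1 | 0.1084 | 0.1034 | 80.1% |
| 2:1 | 0.1142 | 0.1100 | 75.6% |
| 3:1 | 0.1234 | 0.1198 | 68.6% |

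The direction of the imbalance matters little: with the higher-glucose group as the smaller quarter, power is 68.3%. At 2:1, the difference detectable with 80% power is 31.6 points instead of 30. Restoring 80% for a 30-point difference would need about 95 or 96 evaluable patients, or 112 to 113 enrolled (95 / 0.85 and 96 / 0.85, rounded up).

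**4. Adjustment.** If covariates explain a share R² of the variation in glucose group, the effective number is about 85·(1 − R²). R² is an assumption; the article gives no value.

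| R² | Effective N | Power at 1:1 | Power at 2:1 |
|---|---|---|---|
| 0.1 | 76.5 | 75.7% | 71.0% |
| 0.2 | 68.0 | 70.5% | 65.7% |
| 0.3 | 59.5 | 64.5% | 59.7% |

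**5. Continuous glucose in the logistic model.** Odds ratio per SD detectable with 80% power = exp[2.80 / √(85·0.51·0.49·(1 − R²))]. This gives 1.84 unadjusted, 1.97 at R² = 0.2 and 2.07 at R² = 0.3.

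Whether the plan's assumed effect exceeds these values depends on its shape. Simulations with 85 patients, a 2:1 split and a likelihood-ratio test adjusted for one covariate (R² 0 to 0.3) gave:

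- **Normal glucose, log-linear effect:** 0.66 v 0.36 corresponds to an odds ratio of about 2.24 per SD, and power is about 80% to 93%.
- **Pure step at the cut, glucose still entered as continuous:** power is about 39% to 56%.

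**The case against.** The strongest defence has four parts.

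- **The number is correct.** It is: 50 per group reproduces, and this is not an arithmetic error.
- **A reader might infer that the study is underpowered, and the documents do not support that.** The analysis section speaks of glucose levels, not of a dichotomy. Under a log-linear effect of the assumed size, an adjusted continuous model keeps about 80% power or more over the range of R² tried. A step effect would give much less, but the article reports neither a glucose distribution nor an effect shape, so a general shortfall cannot be asserted.
- **A reader might take two-thirds as the expected split, and this also goes too far.** That figure describes poststroke hyperglycaemia in ischaemic stroke generally. It is not tied to 155 mg/dL, to thrombectomy patients or to the moment of reperfusion. The 2:1 row is therefore an assumption, and the loss there is modest without adjustment: 80.1 − 75.6 = 4.5 points.
- **Simple sizing is common and the article is cautious.** Comparing outcome by glucose and glucose by outcome are two views of one association, and a two-proportion test is a usual approximation. The section concedes that earlier studies do not permit a formal calculation. The article lists small sample size as a limitation, and the full protocol may define the groups.

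These points limit the concern but do not remove it. After its caveat, the section still states explicit error rates for two unnamed groups of equal size, which nothing in the design secures. The analysis described next is a different one.

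**Conclusion.** The concern holds in a limited form. The stated 80% power is valid for an equal split and an unadjusted comparison of 0.66 with 0.36. It does not describe a design in which glucose is observed, the groups and the control are undefined, and the stated model is adjusted.

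For a two-group contrast with 85 evaluable patients, power runs from 80.1% at 1:1 to about 68.6% at 3:1, and lower with adjustment. These figures rest on a two-sided alpha, on 0.66 belonging to the higher-glucose group, and on assumed splits and R² values. For continuous glucose the direction of the discrepancy is unknown.

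Severity is moderate. The sample size need not change and the planned model is not invalidated. What needs correcting is the power statement and its link to the primary contrast.

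**What to change.** Keep 100 patients and revise the Sample size estimates section:

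1. Define the two groups and say which one carries the rate of 0.66.
2. Name one primary contrast that matches the logistic model in Statistical analysis.
3. Replace the statement of 50 per group with a beta risk of 0.20 by two items: power for the 155 mg/dL contrast over splits from 1:1 to 3:1, and the detectable odds ratio per SD of glucose in the adjusted model at about 85 evaluable patients (about 1.84 unadjusted; 1.97 to 2.07 for assumed R² of 0.2 to 0.3). Label the splits and R² values as assumptions.
4. Have the recalculation after 50 patients use the observed glucose split as well as the sensor-failure rate, to restate power.

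The cost is a rewritten paragraph and no extra patients. The stated power will look less favourable if the split turns out unequal.
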